### Recruitment

Recruitment will occur in Azienda Ospedaliero-Universitaria Maggiore della Carità di Novara. Enrolment will be proposed to eligible subjects by clinical neurologists during routine visits and given their recorded consent to receive information about ongoing research and recruiting trials. Patients will be recruited continuously until reaching the desired sample size and will start the trial period asynchronously. The recruitment period will be limited in time to avoid seasonal diet modifications as a confounding factor for some of the trial outcomes.

### Assignment of interventions

#### Allocation

Participants will be assigned to the two intervention arms using the minimisation method, with a 1:1 allocation ratio. Codes for the two arms of the study will be different, but investigators, clinical, and laboratory staff will not know which code is assigned to the placebo or intervention group. This assignation method will minimise predictable differences between the two groups (e.g., sex, age). Packages for the treatment formulation and placebo will be identical and although treatment and placebo packages will be differently coded, participants, clinicians, and all laboratory operators will be blinded to the coding scheme.

#### Blinding

Trial participants, care providers, outcome assessors, and data analysts will be blinded to treatment allocation. Only the provider of the treatment and placebo packages will know the coding schemes for the corresponding packages and will not disclose this information until after trial completion.

No unblinding procedure is needed. Participants will be advised to report any suspected adverse reaction and new or worsening symptoms. Every report will be recorded, and a thorough evaluation will be performed by clinical staff. Feedback will be provided to the participant as well as indications on continuing or stopping treatment administration, without unblinding the subject’s allocation.

### Data collection and management

#### Plans for assessment and collection of outcomes

Collected data will include clinical scales and questionnaires, administered by trained clinical neurologists at baseline visit T0, visit T1, and visit T2, and data from analyses carried out by trained technicians and laboratory staff on faecal samples and whole blood samples collected at T0 and T2.

Blood specimen processing protocols are available from the corresponding author upon request. Follow-up visits will be scheduled at 6 weeks after T0 (T1) and at 12 weeks after T0 (T2). At T1, physical and neurological examination will be repeated, and all clinical scales administered again, except for Bristol Stool Form Chart and MOCA. At T2, all assessments performed at T0 will be carried out again, including blood withdrawal.

At T0 and T2, withdrawal of 40 ml venous blood will be performed after a fasting night, between 8:00 and 10:00 am, in EDTA-coated tubes (BD Vacutainer). Tubes will be subsequently coded and stored at room temperature until processing, which will occur within 24 h after collection. A complete blood count with differential analysis will be conducted on separate blood samples.

### Brief description of protocols for endpoint assessment

#### Plasma cytokine measurement

The possible influence of probiotic treatment on the inflammatory profile will be evaluated by measuring at T0 and T2 the plasma levels of pro (e.g., TNF-α, IFN-γ) and anti-inflammatory cytokines (IL-10, IL-4). To this end, at each visit time, plasma aliquots from every sample will be separated and stored for cytokines assays (ELISA Ready-SET-Go! Affymetrix eBioscience, USA). Two milliliters of fresh blood will be centrifuged at 1400g for 10 min at room temperature and two plasma aliquots of 350 µL each will be stored in 1.5mL vials to assay extracellular cytokines levels.

#### ROS production

The production of ROS will be assessed using the superoxide dismutase-sensitive cytochrome C reduction assay, as nmol of reduced cytochrome C/10^6^ cells/30 min, using an extinction coefficient of 21.1 mM. RPMI 1640 without phenol red and FBS will be used for incubating cells in order to avoid any spectrophotometric interference.

#### Flow cytometric evaluation of immune phenotype

For FACS assays of immune phenotype, 5 mL of the peripheral venous blood will be collected, and 100 or 150 µL aliquots of whole blood samples will be incubated with a cocktail of anti-human antibodies (ab) specific for each evaluated cell subset. For naïve-memory cell subset, samples will be stained with anti-human CD45, CD3, CD4, CD8, CD45RA, and CCR7 ab for the identification of naïve (CD45RA+CCR7+), central memory (Tcm, CD45RA-CCR7+), effector memory (Tem, CD45RA-CCR7-), and effector memory RA+ (Temra, CD45RA+CCR7-) on CD3+CD4+ and CD3+CD8+ lymphocytes. CD4+ T helper subsets will be assessed by staining the whole blood sample with a cocktail of anti-human CD45, CD3, CD4, CXCR3, CCR4, and CCR6 ab for the identification of Th1 cells (CD3+CD4+CXCR3+CCR4-CCR6-), Th2 cells (CD3+CD4+CXCR3-CCR4+CCR6-), Th17 cells (CD3+CD4+CXCR3-CCR4+CCR6+), and Th1-Th17 cells (CD3+CD4+CXCR3+CCR4-CCR6+).

Total CD4+ regulatory T cells (cTreg, CD3+CD4+CD25highCD127low) and naïve (nTreg, CD3+CD4+CD25highCD127lowCD45RA+), activated (aTreg, CD3+CD4+CD25highCD127lowCD45RA-) Treg will be evaluated by incubating whole blood with the following ab: CD45, CD3, CD4, CD25, CD127, and CD45RA. The aliquot of the blood for the evaluation of monocytes will be incubated with a cocktail of anti-human CD45, HLA-DR, CD14, and CD16 ab for the identification of classical (HLA-DR+CD14highCD16-), non-classical (HLA-DR+CD14lowCD16high), and intermediate (HLA-DR+CD14highCD16+) monocytes. Finally, another aliquot of whole blood samples will be stained with a cocktail of anti-human CD45, CD3, CD56, and CD57 for the identification of total NK cells (CD3-CD56+) and their two main subsets: CD56dim (CD3-CD56dimCD16bright) and CD56bright (CD3-CD56brightCD16dim), together with the evaluation of the maturation marker CD57. The acquisition will be performed on a BD FACS Celesta flow cytometer (Becton Dickinson Italy, Milan, Italy) with BD FACS Diva software (version 8.0.1.1) and data will be analysed with FlowJo software (version 10.7.1).

#### Transcriptional factors mRNA evaluation

According to our previous studies (Kustrimovic et al., 2018; De Francesco et al., 2021), we aim to investigate whether probiotic treatment is also able to modify the mRNA levels of the main transcriptional factors in CD4+ T lymphocytes. To this end, CD4-positive cells will be obtained by PBMC, which will be separated from whole blood using Ficoll-Paque Plus density gradient centrifugation. After resuspension, any residual contaminating erythrocytes will be lysed by the addition of 10 mL of lysis buffer ((g/L) NH4Cl 8.248, KHCO_3_ 1.0, EDTA 0.0368). Cells will be washed twice in PBS by the addition of 10 mL of PBS, then centrifuged at 300 g for 10 min at RT and resuspended in 10 mL of RPMI/10% FBS. A manual cell count will then be performed to set CD4 separation reagent quantities. Typical PBMC preparations will contain at least 80% lymphocytes. CD4^+^ T cells will then be isolated from PBMC by means of Dynabeads CD4-Positive Isolation kit. At least 50,000 separated CD4^+^ T cells will then be resuspended in PerfectPure RNA lysis buffer (5 Prime GmbH, Hamburg, Germany), and the total RNA will be extracted by PerfectPure RNA Cell Kit™. Reverse-transcription will be performed on the resulting mRNA using a random primer and a high-capacity cDNA RT kit. Real-Time PCR reactions will be performed with 1 μM cDNA. Amplification of cDNA will allow for the analysis of mRNA levels of the transcription factor genes TBX21, STAT1, STAT3, STAT4, STAT6, RORC, GATA3, FOXP3, and NR4A2.

#### Motor and non-motor symptoms, quality of life monitoring

The clinical evaluation will be completed by the administration of forms and questionnaires. In particular, every participant will fill out the forms and questionnaires listed in the following Table 5 at T0, T1, and T2. Data from these scales will be used to monitor motor and non-motor symptoms and perceived quality of life during the trial.

**Table 5 Tab5:** Clinical scales for the assessment of motor and non-motor symptoms and quality of life monitoring

**Clinical scale**	**Reference (DOI)**
Unified Parkinson’s disease rating scale (UPDRS)	10.1002/mds.10473
Hoehn and Yahr assessment (H&Y)	10.1002/mds.20213
Zung self-rating anxiety scale	10.1016/S0033-3182(71)71479-0
Beck depression inventory scale (BDI-II)	10.1002/mds.20792
Composite autonomic symptoms scale-31 (COMPASS 31)	10.1016/j.mayocp.2012.10.013
Montreal cognitive assessment (MOCA)	10.1590/1980-57642018dn13-010008
Patient assessment of constipation (PAC-QoL)	10.1080/00365520510012208
Non-motor symptoms scale (NMSS)	10.1111/ane.13336
Wexner scale	10.1007/BF02056950
Constipation assessment scale (CAS)	10.12968/ijpn.2012.18.7.321

### Plans to promote participant retention and complete follow-up

Participants will be contacted by phone to timely schedule T1 and T2 visits. Any intercurrent health issue will be recorded and evaluated by clinical neurologists, who will assess the need to drop the subject from the study protocol. Any previously collected data will be kept after dropout and used as appropriate in statistical analyses.

### Data management and confidentiality

Data for all participants will be recorded by clinical staff at the enrolment location at scheduled visits. Every entry will be double-checked by at least two different investigators and data will be monitored upon collection to evaluate the consistency and promote early identification of abnormal outliers.

Personal information about trial participants will be strictly confidential and managed by clinical staff at the enrolment location. Investigators who will manage collected specimens and perform data analyses will be blinded to the subjects’ identity. Every collected sample will be assigned a unique code, which will be used by all non-clinical investigators for specimen identification. Clinical staff will ensure the confidentiality of participants’ data.

### Plans for collection, laboratory evaluation, and storage of biological specimens for genetic or molecular analysis in this trial/future use

All laboratory analyses will be executed after storage of specimens at −80°C, performing batches of sample analyses. Every sample in storage journals will be identified with an anonymised code.

### Statistical methods

#### Statistical methods for outcome evaluation

To assess the main trial feasibility, the drop-out rate will be reported as the absolute number and percentage of total participants for both the intervention and placebo arms and will be accounted for when assessing an appropriate sample size for the main study. Feasibility will also be evaluated by recording all drop-out reasons and accordingly estimating an increase of the foreseen sample size.

Collected results will be reported as mean ± standard deviation (SD) of the mean, or median ± 25th and 75th percentile, as appropriate, and *n*, with *n* indicating the number of observations. The normality of data distribution will be analysed by means of D’Agostino-Pearson omnibus normality test. Mann–Whitney *U* test, Wilcoxon test, and Kruskal-Wallis tests will be used to assess differences in the distribution of non-parametric data. Paired and unpaired *t* tests will be used, as appropriate, to compare means and standard deviations for parametric data in the two treatment groups. Wilcoxon signed ranks test will be used to compare measures taken at T0 with the corresponding measures at T1 and T2 in the assessment of primary and secondary outcomes. When appropriate, efficacy outcomes will be reported as estimates with 95% confidence intervals. Statistical significance for correlations will be set at *p*<0.05. Commercial software (GraphPad Prism version 9.3.0 for Windows, GraphPad Software, San Diego, CA, USA, www.graphpad.com) will be used for data analyses and graph plotting.

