In order to investigate possible changes in immune phenotype, we plan to deepen the profile of both innate and adaptive immunity by means of a cytofluorimetric evaluation, according to the strategy described by Kustrimovic et al. (2018) and with additional panels specifically dedicated to innate immunity. The following cell subsets of the adaptive immune system will be assessed: CD4+ and CD8+ T naïve/memory cells, CD4+ T helper subsets (Th1, Th2, and Th17), and CD4+ regulatory T cells (conventional, naïve, and activated Treg). Moreover, for innate immunity, monocytes (classical, non-classical, and intermediate), and NK cells (NK CD56 dim and CD56 bright) will be also assessed. We will compare pre-treatment and post-treatment analysis and compare our intervention group with the placebo group at T0 and T2.

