### Sample size

The design of this pilot study is explorative and equally randomised to treatment with probiotics or placebo. Due to the exploratory nature of the proposed study, a formal sample size calculation is not strictly required [18]. In our precedent in vitro study, statistically significant results were found in a small cohort of 40 PD patients for all tested probiotic strains, with a global reduction in proinflammatory cytokines production and an increase in anti-inflammatory cytokines. Doubling this sample size, with at least 80 specimens to be collected at both T0 and T2, will allow us to correctly evaluate the feasibility of the future main study.

We thus used data from the said study to estimate sample sizes for the in vitro effect of all tested probiotic strains and a sample size of 80 subjects allows for the determination of most tested cytokines variations with an expected power greater than 80%, setting our threshold for statistical significance at 0.05.

As previously stated, the drop-out rate of this pilot study will also be recorded and used to determine an appropriate sample size increase for the main study.

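### The analysis of the laboratory outcomes is not fixed in advance: a normality test on the sample picks the test, no scale is named, and the T0-T2 comparison is given two tests

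*Protocol article*

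**What the plan says.** All of this stands in the protocol article.

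- **Choice of test** (Statistical methods for outcome evaluation): "The normality of data distribution will be analysed by means of" the D'Agostino-Pearson omnibus test. Mann-Whitney, Wilcoxon and "Kruskal-Wallis tests will be used to assess differences in the distribution of non-parametric data". Paired and unpaired t tests serve "to compare means and standard deviations for parametric data in the two treatment groups". No transformation is stated or excluded.
- **T0 comparisons** (same paragraph, with no condition attached): "Wilcoxon signed ranks test will be used to compare measures taken at T0 with the corresponding measures at T1 and T2", for primary and secondary outcomes.
- **Summary statistics** (same paragraph): "Collected results will be reported as mean ± standard deviation (SD) of the mean", or median with quartiles.
- **Comparisons** (Primary feasibility outcomes, immune-phenotype paragraph): "We will compare pre-treatment and post-treatment analysis and compare our intervention group with the placebo group at T0 and T2".
- **Timing** (Plasma cytokine measurement): "measuring at T0 and T2 the plasma levels of pro" and anti-inflammatory cytokines. Blood is drawn only at T0 and T2.
- **Expected direction** (Sample size): the earlier in vitro work found "a global reduction in proinflammatory cytokines production and an increase in anti-inflammatory cytokines". The Background adds a fall in ROS.
- **Use of the results** (Table 1; Primary feasibility outcomes): the main trial's primary outcome is to be chosen among the immune measures that change significantly, and the pilot data are to size that trial.

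**The concern.** Three things are left open in a paragraph that should close them.

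1. Whether a measure counts as parametric is decided by the sample. The quantity compared (mean or rank) can therefore differ from one cytokine to the next, partly by chance.
2. The only paired comparisons in the plan are T0 with T1 or T2. A measure that passes the normality test has a paired t test under one sentence and a Wilcoxon test under the next.
3. Cytokine concentrations, ROS per million cells and mRNA levels are positive quantities for which proportional change is natural, yet no scale is fixed. On the raw scale, a T0-T2 difference is driven by patients with high starting values.

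Significance is the rule for choosing the main trial's outcome, so an ambiguous test bears directly on what the pilot has to deliver. The phrase that attaches the SD to the mean adds to this. It can be read as a standard error, whereas sizing the next trial needs the SD of individual values.

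**Working it through.** **The plan's own power figure.** The Sample size section claims more than 80% power with 80 subjects at 0.05 for most cytokines. It gives no effect or SD, so the claim can be neither confirmed nor refuted. What it requires, two-sided, is a standardised effect of:

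- between arms, 40 each: (1.960 + 0.842) × √(2/40) = 0.63
- paired, n = 40: 2.802/√40 = 0.44; paired, n = 80: 2.802/√80 = 0.31

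**Inputs to the simulations.** From the article: 80 subjects, 1:1, alpha 0.05. Assumed, because the article gives no distribution: log-normal values, CV 0.3 to 1.2 (log SD = √ln(1 + CV²), i.e. 0.29 to 0.94) or log SD 0.3 to 1.0 directly; T0-T2 correlation ρ of 0.5 to 0.7; two-sided tests; no dropout. Effects were mostly set so that a log-scale t test has about 80% power:

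- between-arm change: d = 2.802 × log SD × √(2 − 2ρ) × √(2/40). With CV 0.5, ρ = 0.5: 2.802 × 0.472 × 1 × 0.2236 = 0.296, a fall of 25.6% or a rise of 34.4%.
- within one arm: d = 2.802 × log SD × √(2 − 2ρ)/√40. With the same CV and ρ: 0.209, a fall of 18.9%.

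**Two tests for T0-T2.** The paired t and Wilcoxon tests give different significance calls in 6 to 21% of trials when the effect is sized for 80% within-arm power. With the larger effect sized for the between-arm comparison (ρ = 0.6), they disagree in about 1 to 16%. With no effect they disagree in roughly 3%, and counting either as a success gives about 5 to 7% type I error.

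**The normality step alone.** At CV 0.5 it rejects in about 65 to 69% of trials for raw changes, so the test used does vary with the sample. Its type I error is 4 to 6%. Its power tracks the better raw-scale test: at CV 0.8, between-arm raw change, the t test has 0.55, Mann-Whitney 0.63, the two-stage rule 0.63, and a log-scale t test 0.79. The gap to 0.79 comes from differencing on the raw scale, not from the pre-test.

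**Power, plan's rule on raw values against a pre-fixed log t test:**

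| Comparison | Plan's rule | Log t test | Loss over all settings |
|---|---|---|---|
| T2 levels between arms, reduction (CV 0.5) | 0.65 | 0.67 | 0.5 to 3 points |
| T0-T2 within arm, reduction (CV 0.3) | 0.75 | 0.78 | 2 to 10 points (with the next row) |
| T0-T2 within arm, reduction (CV 1.2) | 0.69 | 0.78 | |
| Change between arms, reduction (CV 0.5) | 0.68 | 0.79 | 6 to 20 points (with the next row) |
| Change between arms, reduction (CV 0.8) | 0.63 | 0.79 | |
| Change between arms, increase (CV 0.5 to 0.8) | 0.75 to 0.80 | 0.78 to 0.80 | 0 to 4 points |

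The loss is small for T2 levels because Mann-Whitney is unchanged by a log transform. The direction matters only for between-arm change: one log effect of 0.44 (CV 0.8, ρ = 0.5) is a 35.6% fall or a 55.4% rise, so on the raw scale the fall is the smaller shift. Within an arm, rises and falls lose about the same.

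**Adjusting for baseline.** With ρ = 0.6, the variance of log change is 2(1 − 0.6) = 0.80 and that of log T2 given log T0 is 1 − 0.36 = 0.64, in units of log SD². An effect with 80% power on log change then has power Φ(2.802 × √(0.80/0.64) − 1.960) = Φ(1.17) = 0.88. Simulation gave 86 to 88%, against 60 to 73% for the plan's rule on raw change and 66 to 71% on T2 levels.

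**Where the log scale does not help.** With normal raw data at CV 0.3, the log t test has 0.77 against 0.80 for the plan's rule. With 20% of values undetectable and set to half the limit, log t falls to about 0.72, still above the plan's 0.61 to 0.67.

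**The case against.** The strongest reply has four parts.

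- **The large loss belongs to a comparison that the article does not fix.** The one sentence that spells out comparisons names before-after and arm against arm at T0 and T2. For T2 levels the loss is 0.5 to 3 points. This stands. Between-arm change is still a fair reading, because the abstract defines the primary endpoint as changes in cytokines and ROS, and the outcomes section looks for variation between the two arms.
- **The normality step is harmless.** A reader might infer that choosing the test by a pre-test inflates type I error or wastes power. The calculations do not support that. The objection to it is that the compared quantity is left to the sample.
- **The raw scale and the skewness are not in the text.** A reader might take the article to prescribe raw-scale analysis. It names no transformation and rules none out, and it provides for medians and rank tests. A condensed article may leave such detail to the full protocol, so silence on scale or on undetectable values is not an error in itself. What the article does state is the pre-test rule and two overlapping tests for T0-T2; that needs no distributional assumption.
- **Log-normal simulations favour a log analysis by construction.** This is true. The claim that a log analysis costs nothing would be wrong: it costs about 3 points if raw data are near normal. IL-4 and IL-10 are expected to rise, where between-arm change loses little.

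The exploratory aim lowers the stakes but does not remove them, since the next trial's outcome is selected from these tests.

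**Conclusion.** The point holds in a limited form. The article lets the sample choose the test, fixes no scale for the laboratory measures, and assigns two tests to T0-T2. The double assignment is a contradiction within one paragraph and stands whatever the distribution. Its cost is discretion: about 1 to 21% discordant calls when an effect exists, and 5 to 7% type I error if the better result is taken, which nothing in the article says will happen.

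The power loss is conditional. It needs right-skewed measures compared as raw differences, and its size depends on which comparison is made. No single loss figure can be attached to the plan. It should be settled before unblinding, because the pilot's choice of outcome depends on it.

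**What to change.** In Statistical methods for outcome evaluation:

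1. For IFN-γ, TNF-α, IL-4, IL-10, ROS and mRNA only, name one between-arm analysis in advance: log T2 with log T0 as covariate, reported as a ratio of geometric means with 95% CI. Keep rank tests as a sensitivity analysis and state one rule for values below the assay limit.
2. Name a single test for T0-T2 and remove the overlap.
3. Keep a stated test for the clinical scales and cell subsets, so that dropping the normality step for the laboratory measures leaves no gap there.
4. Report the SD of individual log changes by arm for sizing the main trial, and remove the words that tie the SD to the mean.

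This changes wording only and needs no new data. The article plans no interim analysis of collected data and keeps analysts blinded, so it can still be set before unblinding. The price is that results are expressed as ratios, undetectable values need a rule, and about 3 points of power are lost if a measure turns out near normal on the raw scale.

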#### Interventions

This is a placebo-controlled trial. The intervention group will be treated with a daily dose of probiotics, while the control group will be given identical packages containing maltodextrin only, used as a bulking agent in the probiotics’ formulation for the intervention group. In this pilot study, our aim is to assess the potential of probiotics therapy to modify the peripheral immune system profile and function in a cohort of PD subjects. In this pilot trial, the potential immunomodulating effects of probiotics will be tested. Placebo treatment was chosen as a comparator for this new approach to immunomodulation in PD.

During the enrolment visit, the medical and neurological examination will assess the need for immediate variations in medical therapy for each participant. Within 2 weeks, any therapy modification will be completed, and a baseline visit will be scheduled.

During the baseline visit (T0), physical and neurological examinations will be repeated to confirm the subject’s conditions and persistence of inclusion criteria, a baseline blood withdrawal will be performed, and all clinical evaluation scales will be completed to set baseline scores. Each participant, after the subscription of an appropriate informed consent, will be randomised and given a treatment box, containing single-dose sachets with 2.7g of powder of the allocated formulation. Patients will be instructed to take daily doses at home every morning before breakfast for 12 weeks, mixing the content of one sachet in about 125 ml of fresh water or other cold, non-carbonated drink. Participants will be instructed to keep unused or empty packaging for recollection and compliance evaluation.

Product compositions per dose (1 sachet, 2.7g) for the treatment and placebo compounds are listed in the following Table 3.

**Table 3 Tab3:** Treatment and placebo composition

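### The test tied to the primary and secondary outcomes is a before/after test without a placebo contrast; between-arm tests are listed, but none is named as decisive or adjusted for baseline

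*Protocol article*

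**What the plan says.** The section on statistical methods for outcome evaluation states that the "Wilcoxon signed ranks test will be used to compare measures taken at T0 with the corresponding measures at T1 and T2", and gives the scope of that test as "in the assessment of primary and secondary outcomes".

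The same section lists other tests without tying them to named outcomes. Mann-Whitney, Wilcoxon and Kruskal-Wallis tests "will be used to assess differences in the distribution of non-parametric data". Paired and unpaired t tests serve "to compare means and standard deviations for parametric data in the two treatment groups".

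Four other parts of the protocol bear on the point:

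- **Primary feasibility outcomes.** Main-trial outcomes are to be selected on significant variation between the two arms. For the cell subsets, the plan is a pre/post comparison and also to "compare our intervention group with the placebo group at T0 and T2".
- **Data collection.** Laboratory data come from faecal samples and "whole blood samples collected at T0 and T2". The participant timeline (Table 4) agrees: no blood is drawn at T1.
- **Allocation.** Patients are allocated 1:1 by minimisation: "This assignation method will minimise predictable differences between the two groups (e.g., sex, age" being the examples given.
- **Interventions.** Antiparkinsonian therapy may be adjusted between enrolment and T0: "Within 2 weeks, any therapy modification will be completed, and a baseline visit will be scheduled".

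**The concern.** A signed-rank test of T0 against a later visit asks whether patients changed. It does not ask whether probiotic patients changed more than placebo patients. The text does not say whether the test is run in each arm or on all patients together, but neither version contrasts the arms.

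The T1 part cannot be carried out as written for the outcomes that the abstract calls primary (cytokines, ROS) and secondary (lymphocyte subpopulations, transcription-factor mRNA). All of these need blood. Only the clinical scales, which the protocol treats as exploratory, have T1 values.

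The between-arm comparisons are loosely specified. A comparison at T0 is uninformative about treatment, because any difference there arose by chance in allocation. A comparison at T2 alone ignores a baseline that has already been paid for. No listed test can take a covariate, although minimisation is used.

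The pilot is meant to pick the main trial's primary outcome and to supply its sample size. A signal produced by drift in both arms would be carried into that design.

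**Working it through.** **1. The plan's own figure.** The sample size section claims power above 80% with 80 subjects at a threshold of 0.05. It gives no effect size, SD or test, so the claim can be neither reproduced nor refuted. It can be solved backwards for 80% power (two-sided 0.05 assumed, z-sum 1.960 + 0.842 = 2.802):

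- between arms, 40 per arm: 2.802 × √(2/40) = 0.626 SD;
- paired, one arm of 40: 2.802 / √40 = 0.443 SD of change;
- paired, all 80: 2.802 / √80 = 0.313 SD of change.

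What the power claim means therefore depends on which test decides.

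**2. Common drift and no treatment effect.** Inputs: 40 per arm (80 at 1:1, from the protocol). Assumed, because the protocol gives no values: drift of 0.2 to 0.5 outcome SD, equal in both arms; T0-T2 correlation ρ = 0.5; normal data. The SD of change is √(2(1 − ρ)) = 1 outcome SD. Results from 4,000 simulated trials per row:

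| Drift (SD) | Probiotic arm signed-rank p < 0.05 | Probiotic significant, placebo not | Mann-Whitney on change |
|---|---|---|---|
| 0 | 4.6% | 4.4% | 4.7% |
| 0.2 | 22.5% | 17.4% | 4.3% |
| 0.3 | 44.4% | 24.8% | 4.9% |
| 0.4 | 67.8% | 22.8% | 4.7% |
| 0.5 | 85.7% | 12.8% | 5.8% |

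Two checks:

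- The paired normal approximation Φ(d√40 − 1.96) gives 47.5%, 71.6% and 88.5% at d = 0.3, 0.4 and 0.5. This is slightly above the signed-rank results, as expected.
- With independent arms, the third column should equal p(1 − p): 0.225 × 0.775 = 17.4%, 0.444 × 0.556 = 24.7%, 0.678 × 0.322 = 21.8%, 0.857 × 0.143 = 12.3%. It cannot exceed 25%, reached at p = 0.5.

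At ρ = 0.7 the second column is 35.6%, 67.2%, 87.7% and 97.1% for drifts of 0.2 to 0.5, and the third is 23.8%, 24.0%, 11.0% and 2.2%.

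**3. Value of the baseline.** Relative to an unadjusted T2 comparison, ANCOVA on T0 has variance factor 1 − ρ². A comparison of change scores has factor 2(1 − ρ). For assumed ρ = 0.3 / 0.5 / 0.7:

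- ANCOVA factor: 0.91 / 0.75 / 0.51, a cut of 9% / 25% / 49%;
- effect detectable at 80% power, 0.626 × √(1 − ρ²): 0.598 / 0.543 / 0.447 SD;
- power for an assumed 0.5 SD effect: 60.9% unadjusted, then 65.0% / 73.3% / 87.9%;
- ANCOVA against change scores, (1 − ρ²) / (2(1 − ρ)) = (1 + ρ)/2: 0.65 / 0.75 / 0.85.

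So even if the listed tests were applied to changes, adjustment would still cut variance by 35% / 25% / 15%.

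**The case against.** A reader might infer that the plan has no between-arm test, or that a significant change on probiotic with none on placebo will be called efficacy. The protocol does not support either. It lists unpaired t and Mann-Whitney tests, and its criterion for choosing main-trial outcomes is a difference between arms. Drift misleads only if the before/after test is taken as the efficacy result. What remains is that this test is the one assigned by name to the primary and secondary outcomes, and no sentence ranks the two kinds of test.

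The drift sources should not be overstated either. Recruitment is to be limited in time to avoid seasonal diet changes, so enrolment across seasons cannot be assumed. Specimens are to be analysed in batches after frozen storage, so samples taken 12 weeks apart need not be assayed 12 weeks apart. Therapy adjustment shortly before T0 and vaccination, which the discussion section plans to record, remain plausible; neither is quantified.

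The sentence comparing arms at T0 and T2 concerns cell subsets and names no test. The unpaired tests could be applied to changes from T0, which would remove common drift; the protocol neither says so nor excludes it. Kruskal-Wallis with two arms is redundant next to Mann-Whitney, not invalid.

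Finally, unadjusted randomised comparisons are valid, and ignoring minimisation factors tends to be conservative. Model detail is commonly left to an analysis plan. That would answer a complaint about missing detail, but here the article itself fixes the tests, and the test it attaches to the main outcomes has no treatment contrast.

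**Conclusion.** The point holds as an ambiguity about which test decides, together with an avoidable loss of precision. The named before/after test cannot show a probiotic effect and cannot be run at T1 on blood outcomes.

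Read as efficacy, it would be significant in the probiotic arm in about 23% to 86% of trials under the assumed 0.2 to 0.5 SD drift and ρ = 0.5, with no true effect. The pattern of probiotic significant and placebo not would arise in about 12% to 25%. A between-arm test of change stays near 5%. With no drift there is no such inflation in the single-arm test.

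The precision gain of 25% (9% to 49%) applies against a T2-only comparison and rests on an assumed correlation. The gain from adjusting for the minimisation factors cannot be sized from the protocol. The stated power is unverifiable, not shown to be wrong. For an exploratory pilot whose stated aim is feasibility, this should be fixed but does not undermine the trial.

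**What to change.** Replace the signed-rank sentence with wording to this effect: *For each outcome, the deciding comparison is probiotic versus placebo at T2, adjusted for the T0 value and all minimisation factors, on a log or rank scale where the data are skewed, reported as an estimate with a 95% confidence interval. Before/after comparisons are descriptive.*

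Also:

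- limit T1 analyses to the clinical scales collected at that visit;
- drop significance tests between arms at T0 and describe baseline instead;
- list the minimisation factors in full, so that the adjustment set is fixed.

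The cost is wording and slightly more analysis. T0 values are already collected and the minimisation factors are known at allocation, so no extra patients, visits or assays are needed.
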